## Abstract

**Background:**

Brain arteriovenous malformation (AVM) is an important cause of hemorrhagic stroke in young adults, which can lead to severe neurological impairment. The registry of Multimodality treatment for brain ArTeriovenous malformation in mainland CHina (MATCH) is a national prospective registry to identify the natural history of AVMs in Asian population; to investigate traditional and emerging hemorrhagic predictors; and to explore the superiority of the multidisciplinary assessment in improving the long-term outcomes.

**Methods:**

Consecutive AVM patients will be enrolled from 52 participating hospitals in mainland China. Baseline demographic, clinical and imaging data will be collected prospectively. Conservation, microsurgery, embolization, stereotactic radiosurgery (SRS), and multimodal strategies are all included in this study. Patients will be divided into experimental and control group according to whether the treatment protocols are formulated by multidisciplinary team. Neurofunctional status, subsequent hemorrhage, seizure, and novel neurofunctional deficit will be queried at 3 months, annually (1 and 2 years), 3 years, and 10 years follow-up.

**Results:**

Between August 2011 and April 2021, 3241 AVMs were enrolled in 11 participating sites. Among them, 59.0% were male with an average age of 28.4 ± 14.6 years, 61.2% had rupture history and 2268 hemorrhagic events occurred before admission. The median Spetzler-Martin grade and Lawton-Young grade was 3 and 5, respectively. Microsurgery is the dominant strategy (35.7%), with a similar proportion of embolization, SRS, and a combination of both (12.7%; 14.8%; 11.8%; respectively). Among them, 15.43% underwent multidisciplinary assessment and received standardized treatment. At the most recent follow-up, 7.8% were lost and the median follow-up duration was 5.6 years.

**Conclusions:**

The MATCH study is a large-sample nationwide prospective registry to investigate multimodality management strategy for AVMs. Data from this registry may also provide the opportunity for individualized risk assessment and the development of optimal individual management strategies.

**Trial registration:**

ClinicalTrials.gov Registry (NCT04572568).

**Supplementary Information:**

The online version contains supplementary material available at 10.1186/s41016-022-00296-y.

## Background

Brain arteriovenous malformations (AVMs) are tangles of abnormally dilated vessels without intervening capillaries, which represent high-flow and low-resistance hemodynamic features due to direct arteriovenous shunting [1]. AVMs usually manifest as intracranial hemorrhage (30–70%), seizure (10–30%), headache, or incidental findings (0–15%) [2]. The natural annualized rupture risk of AVMs was estimated to 1–3% per year if left untreated [3]. Non-White race was suggested as an independent hemorrhagic factor in a widely accepted prediction model [4]. However, the finding have not been confirmed in the predominantly yellow Asian population, and some scholars have expressed concerns about it [5]. Therefore, clarifying the natural history of AVMs among Asian populations is of distinct practical significance [6].

The primary purpose of treatment in AVMs is to avoid neurological impairment due to future hemorrhagic stroke [7]. The scientific statement of AHA/ASA proposed that the definitive treatment of AVMs should be complete elimination of the nidus and the arteriovenous shunt [8]. Three interventional modalities have been developed: microsurgery, embolization, and stereotactic radiosurgery (SRS). The Spetzler-Martin (SM) grading system is widely used to estimate the risk of morbidity and mortality attending the operative treatment [9]. Generally, SM I/II AVMs are amenable to microsurgery alone. Embolization and SRS also have been indicated can achieve favorable outcomes with limited morbidity and mortality. SM III AVMs typically require multimodal approach. SM IV/V AVMs must be treated conservatively unless ruptured [10]. In 2014 and 2020, A Randomized Trial of Unruptured Brain Arteriovenous Malformations (ARUBA) concluded that the natural history of unruptured AVMs is better than any form of treatment [11, 12]. Despite the enormous controversy, this result still significantly altered the treatment decision for AVMs [13]. However, conservation of unruptured AVMs assessed as high rupture risk might not be justified. Since the neurological impairment caused by AVM rupture can be fatal, individualized rupture and prognostic prediction models are required to determine whether to take interventions. A recently released expert consensus on the management of AVMs recommends that a multidisciplinary professional committee of neurosurgeons specializing in AVM resection, embolization, and radiation conduct multimodal assessments and create individualized treatment strategies [10].

We conducted this study to identify the natural history of AVMs in the Asian population, investigate the traditional and emerging hemorrhagic predictors, and explore the superiority of the multidisciplinary assessment in improving the long-term outcomes. In this report, we introduced the design, rationale, baseline data, as well as the strengths and potential limitations of the study.

## Methods

### Overview of the MATCH study

The registry of Multimodality treatment for brain ArTeriovenous malformation in mainland CHina (MATCH) is a national multicenter prospective registry that recruited consecutive AVMs from 52 tertiary hospitals that cover 20 provinces, 4 ethnic minority autonomous regions, and 4 municipalities in mainland China. An organizing committee composed of members from Beijing Tiantan Hospital and several neurosurgical centers prepared the design and organization. About 100 tertiary hospitals (about 4 in each province) that can cover most of the population in mainland China passed the initial screening by the MATCH Research Organizing Committee. About 60 hospitals were initially invited, and 52 hospitals were finally identified, which declared that they had reliable research capabilities and were willing to devote themselves to this study. A full list of MATCH study members can be found in Supplementary material 1, and Fig. 1 shows the geographical location of all participating hospitals.

**Fig. 1 Fig1:**
[figure not shown]
The geographical locations of participating sites in MATCH

The main objectives of this study are to identify the natural history of AVMs in the Asian population, investigate traditional and emerging hemorrhagic predictors, and explore the superiority of the multidisciplinary assessment in improving the long-term outcomes. Individuals who complete baseline demographic, clinical, and imaging data collection will be included in the prospective cohort and will be followed up for at least 3 years. This study will last for 20 years, and cross-sectional and longitudinal designs will be used for data analysis on different research topics.

### Study objectives

The objectives of the MATCH study were to identify the natural history of AVMs in the Asian population; to investigate the traditional and emerging angioarchitecture, hemodynamic, genetic, and environmental risk factors associated with AVM rupture; and to explore the superiority of the multidisciplinary assessment in improving the long-term outcomes. Based on this, individualized rupture and prognostic prediction models will be established to promote the precision medicine.

### Study design

This study is a national multicenter prospective registry study. First, the MATCH study will analyze the natural history of AVMs in the Asian population through a Real-World study, explore the relevant factors affecting long-term outcomes through case–control studies, and establish prognostic predictive models. This study will embed nested case-controlled (NCC) studies to explore traditional as well as novel hemorrhagic predictors, and establish reliable predictive models for AVM rupture. The MATCH study will also analyze the superiority of the multidisciplinary assessment in improving the long-term outcomes of AVMs through cohort studies.

### Patient enrollment

All AVMs diagnosed at participating hospitals will be candidates for this study, which is expected to include approximately 4000 AVMs between August 1, 2011 and April 1, 2032. The inclusion criteria are as follows: (1) the diagnosis of AVM is confirmed with digital subtraction angiography (DSA) and/or magnetic resonance imaging (MRI); (2) patients with complete clinical and imaging data; (3) patients or their guardians agree to collect personal information for this study and sign informed consent. The exclusion criteria are as follows: (1) patients undergo intervention management before admission, such as microsurgery, embolization, or SRS; (2) patients diagnosed with spinal AVMs; (3) patients missing critical baseline demographic, clinical, and imaging data.

### Baseline data collection

The data collection is performed through face-to-face interviews and examinations by centralized trained personnel following a standard data collection protocol developed by the MATCH Research Organizing Committee (Table 1). The information including demographics, medication history, neurological status, laboratory tests, imaging characteristics, and hemodynamic parameters.

**Table 1 Tab1:** Schedule of evaluation in the MATCH study

Characteristics	Screening and Entry	Pre-treatment	Discharge	3 months follow-up	Annual follow-up (1 and 2 years)	3 years follow-up	10 years follow-up
Diagnosis	X						
Written informed consent	X						
Past treatment history	X						
Demographic data	X	X					
Medical history	X	X		X	X	X	X
Medication history		X	X	X	X	X	X
Physical examination	X	X	X	X	X	X	X
Clinical neurofunctional assessment	X	X	X	X	X	X	X
CTA scanning	X	X	X				
MRI scanning	X	X		X	X	X	X
DSA examination	X	X		X		X	X
Hemodynamic evaluation		X		X		X	X
Treatment strategy			X				
Complications			X	X	X	X	X
Obliteration rate			X	X	X	X	X
Hemorrhagic vascular events			X	X	X	X	X

*CTA* Computed Tomography Angiography, *DSA* Digital Substraction Angiography, *MATCH* Registry of Multimodality treatment for brain ArTeriovenous malformation in mainland China, *MRI* Magnetic Resonance Imaging

An electronic data capture (EDC) system has been developed and used for data collection. The patient can be registered via a web-based system that will structure the forgoing characteristics (https://artt.neurochina.com). The EDC system is available 24 h a day and can automatically check the integrity and logical error of the uploaded data. An independent contract research organization will performs regular independent data monitoring through the EDC to troubleshoot and question data where errors exist. All data are anonymized prior to data analysis.

### Demographic and clinical characteristics

The demographic data included sex, ethnicity, admission age, family history, diet, physical activity, educational attainment, lifestyle, smoking status, drinking status, and medication history.

The clinical characteristics included onset manifestation (hemorrhage, seizure, headache, neurofunctional deficit, accidentally discovered, others), admission modified Rankin Scale (mRS), time of each rupture, treatment modalities (conservation, microsurgery, embolization, SRS, multimodality strategy, etc.), discharge obliteration rate, perioperative complications (hemorrhage, seizure, intracranial infection, etc.), discharge mRS, etc. The hemorrhagic presentation is defined as hemorrhage attributable to AVM rupture with symptomatic and CT evidence. Seizure is classified as generalized and partial. The evaluation of mRS was conducted by trained who have at least 5 years of experience in clinical practice.

### Imaging data collection

MRI and DSA are recommended for all AVMs in the MATCH study. For MRI, three-dimensional T1-weighted magnetization prepared rapid acquisition gradient echo (3D T1w MPRAGE), two-dimensional T2-weighted (2D T2w), susceptibility-weighted imaging (SWI), three-dimensional time-of-flight MR angiography (3D-TOF MRA) are included as mandatory sequences at baseline, 3-month, annually (1 and 2 years), 3-year, and 10-year follow-up. Resting-state fMRI and diffusion tensor imaging (DTI) are the recommended sequences for AVMs involving eloquent areas for treatment decision. DSA examination is recommended when evaluating the rupture risk, choosing a treatment strategy, and determining the postoperative obliteration rate. Besides, 3-dimensional DSA is considered necessary if a combined aneurysm is suspected. In terms of hemodynamic assessment, the MATCH study uses color-coded DSA post-processing technique (syngo iFlow, Siemens, Berlin, Germany) to obtain time-dependent hemodynamic parameters [14]. Trained investigators will conduct all the MRI and DSA based on standardized protocol. These imaging techniques enable us to observe angioarchitecture features, screen hemorrhagic predictors, monitor the progression, and assess the risk of secondary hemorrhage. Imaging data were collected in the form of digital images and communications in the form of medical CDs (DICOM format) and analyzed by the Imaging Committee (a multidisciplinary team of Neurosurgery, Interventional Neuroradiology, Radiosurgery, and Imaging Research Center) of the MATCH Research Organizing Committee.

The definition of angiographic characteristics is consistent with the reported terminology provided by the joint committee led by the American Society of Interventional and Therapeutic Neuroradiology [15]. The hemodynamic parameters included time to peak (TTP), inflow gradient, outflow gradient, stasis index, full width at half maximum (FWHM), trans-nidal relative velocity (TRV), etc. [16, 17]. All the angioarchitecture and hemodynamic parameters are independently interpreted manually and double-blind. If there is doubt about interpretation, the Imaging Committee will arbitrate and analyze.

### Clinical management

Conservation, microsurgery, embolization, SRS, and multimodal strategies are all included in this study. Patients will be divided into experimental and control groups according to whether the treatment protocols were formulated by a multidisciplinary team. In order to reduce workload, the MATCH Research Organizing Committee developed a standardized treatment protocol of multidisciplinary assessment as follows:

Ruptured AVMs: (1) microsurgery: microsurgery is recommended for AVMs not located in deep critical eloquent areas (brainstem, thalamus, basal ganglia, etc.) or more than 5 mm away from functional fiber bundles, regardless of the SM grade; (2) embolization: embolization should be performed 2–6 weeks after rupture; target embolization for hemorrhagic predictors could be considered as a monotherapy; palliative embolization can be used as an adjunctive strategy to reduce blood flow or nidus volume before microsurgery or stereotactic SRS; (3) SRS: SRS is indicated for patients with a nidus volume < 10 ml and not in the acute phase of hematoma (< 3 months); volume-stage or dose-stage can be used for giant AVMs. (4) Multimodality: the multimodality strategy such as single-stage combined embolization + resection (hybrid surgery) or staged embolization + resection or adjunctive embolization + resection/SRS or adjuvant SRS + resection are indicated for complex AVMs, such as giant AVMs involving deep eloquent areas, or AVMs with complex blood supply. (5) Conservation: conservation can be used for AVMs that are prone to severe disability due to intervention.

Unruptured AVMs: interventions are recommended if unruptured AVMs are assessed as being at high rupture risk or having refractory epilepsy or acceptable postoperative neurological deficits; otherwise, conservative treatment is recommended. The rupture risk stratification will be assessed qualitatively and quantitatively by the multidisciplinary team based on their own experience and the rupture prediction model to facilitate the division of the experimental and control groups. Regular multidisciplinary discussion meetings and fixed multidisciplinary groupings will ensure consistency of analytical results. Besides, the choice of intervention is the same as for ruptured AVMs.

It should be noted that the AVM multidisciplinary team for the MATCH study was established in June 2018, so the previously collected prospective AVM cohort from August 2011 to June 2018 and the AVM cohort after June 2018 without comprehensive evaluation by the multidisciplinary team served as the control group.

### Follow-up assessment

Neurofunctional status (mRS), subsequent hemorrhage, seizure, headache, novel neurofunctional deficit, and medication were queried at 3 months, annually (1 and 2 years), 3 years, and 10 years follow-up by trained research coordinators. Medical records and imaging examination data will be collected for suspected individuals with cerebral vascular events. An independent final review committee will assess suspected vascular events without hospitalization.

The MATCH study will conduct routine imaging follow-up by MRI, which is consistent with that described above. Due to the dose-cumulative effect, we will use DSA and MRI at the third year to determine the long-term obliteration rate, regardless of the intervention strategies. We will use imaging at 10th year after surgery to assess the ultra-long-term imaging prognosis. Color-coded DSA (follow-up DSA) was used to assess short-term and long-term time-dependent hemodynamic changes in residual nidus, peri-nidus, and cerebral hemispheres after treatment.

### Outcomes measurements

The primary outcome: neurofunctional status (mRS score) at 3 years after treatment. The secondary outcomes: obliteration rate, subsequent hemorrhage, complication rate, and improvement in clinical symptoms (epilepsy, headache, neurological dysfunction) at 3 years after treatment. The obliteration rate will be evaluated by DSA or MRI, as several previous studies have suggested that MRI could provide a similar assessment of the obliteration rate as DSA [18]. The subsequent hemorrhage is defined as intracranial hemorrhage that could be attributed to AVM rupture with symptomatic and CT evidence. Postoperative complication included novel neurological dysfunction, radiation-related complications, etc. The prognosis of epilepsy will be assessed by Engle classification. Post-treatment headache will be assessed by the WHO pain grading classification.

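### The 3-year obliteration outcome is read by DSA and MRI in one section and by DSA or MRI in another, so the reading modality is not fixed across the groups being compared

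*Protocol article*

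**What the plan says.** Outcomes measurements lists obliteration rate first among the secondary outcomes, in a list that ends with "improvement in clinical symptoms (epilepsy, headache, neurological dysfunction) at 3 years after treatment". It then states "The obliteration rate will be evaluated by DSA or MRI", on the ground that "several previous studies have suggested that MRI could provide a similar assessment of the obliteration rate as DSA". It gives no sensitivity, specificity or agreement figure.

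Follow-up assessment describes the same determination differently: "we will use DSA and MRI at the third year to determine the long-term obliteration rate, regardless of the intervention strategies". Table 1 ("Schedule of evaluation in the MATCH study") agrees with that section, marking MRI, DSA and obliteration rate at the 3-year visit.

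Imaging data collection gives the two modalities different standing. It opens by recommending both, then says that the named MRI sequences "are included as mandatory sequences at baseline, 3-month, annually (1 and 2 years), 3-year, and 10-year follow-up". For DSA it says: "DSA examination is recommended when evaluating the rupture risk, choosing a treatment strategy, and determining the postoperative obliteration rate".

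The groups are not randomised. Under Clinical management, the controls are the cohort from August 2011 to June 2018 together with later patients not assessed by the team: "the AVM cohort after June 2018 without comprehensive evaluation by the multidisciplinary team served as the control group".

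**The concern.** The reading method of one outcome at one time point is stated in two ways. If both modalities are used in everyone, the method is uniform. If either suffices, a patient without a 3-year DSA is read on MRI alone and counted with patients read on DSA.

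Nothing then holds the mix of modalities equal between the groups compared. It can vary by treatment, by hospital and by calendar period, and the control group reaches back to 2011 while the multidisciplinary group starts in June 2018. If MRI and DSA differ in how they classify residual nidus, an unequal mix produces an apparent difference in obliteration where none exists. The propensity score matching and weighting in the Statistical analysis section balance baseline covariates. They do not correct an outcome that is measured differently in the two groups.

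**Working it through.** The plan states no sample size, expected obliteration rate or MRI accuracy for this outcome, so there is no figure to reproduce. The check has two parts.

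**1. Can the sections be read together?**

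| Section | 3-year obliteration reading |
|---|---|
| Follow-up assessment | DSA *and* MRI, every strategy |
| Table 1 | MRI and DSA both scheduled |
| Outcomes measurements | DSA *or* MRI |
| Imaging data collection | named MRI sequences mandatory, DSA recommended |

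- One reading is that *or* applies only to the other visits. It fails, because Outcomes measurements sets the secondary outcomes at 3 years.
- Another is that both are scheduled, DSA is recommended, and either is enough to evaluate the outcome. This fits three of the four places, but not the Follow-up assessment statement that both determine the rate. It is also the reading under which modality is left free.

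**2. What could an unequal mix do?** This is an illustration, and every value of *p*, *d*, *se* and *sp* is an assumption.

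Let *p* be the true obliteration rate, equal in both groups. Let *d* be the share read by DSA (taken as the reference), with the rest read by MRI alone. Let *se* and *sp* be the sensitivity and specificity of MRI for residual nidus.

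Observed rate = d·p + (1 − d)·[p·sp + (1 − p)·(1 − se)]

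Spurious difference, group 1 minus group 0 = (d0 − d1)·[(1 − p)(1 − se) − p(1 − sp)]

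Take sp = 0.95, and give group 1 the lower DSA share. False-positive rates use a two-sided 0.05 pooled two-proportion z-test with the 3-year completers in Table 3: 191 multidisciplinary (group 1) and 2181 single-disciplinary (group 0). Those counts agree with the printed percentages: 191/(500 − 49) = 42.4% and 2181/(2741 − 204) = 86.0%.

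| p | se | Bracket | DSA 60% v 80% | False-positive rate | DSA 40% v 90% | False-positive rate |
|---|---|---|---|---|---|---|
| 0.5 | 0.70 | 0.150 − 0.025 = 0.125 | +2.5 points | 0.10 | +6.25 points | 0.38 |
| 0.5 | 0.95 | 0.025 − 0.025 = 0 | 0 | 0.05 | 0 | 0.05 |
| 0.7 | 0.80 | 0.060 − 0.035 = 0.025 | +0.5 points | 0.05 | +1.25 points | 0.06 |
| 0.9 | 0.95 | 0.005 − 0.045 = −0.040 | −0.8 points | 0.07 | −2.0 points | 0.16 |

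Over p from 0.5 to 0.9 and se from 0.70 to 0.95, the first and last rows are the extremes. With d0 = d1, or with se = sp = 1, the difference is 0 and the false-positive rate stays at 0.05.

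The completers may include conservatively managed patients, for whom obliteration is not the aim. The numbers analysed, and hence these false-positive rates, could be smaller.

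**The case against.** The article gives a reason for accepting either modality, namely that MRI performs similarly to DSA. If that holds in this registry, the bias tends to zero, and nothing in the documents shows that MRI is worse. This stands as a limit on the size of the concern. It does not reconcile the sections, since Follow-up assessment still calls for both.

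Table 3 shows a similar treatment mix in the two groups, with no listed treatment type below P = 0.12. Modality use that varied only with treatment would therefore largely balance between the multidisciplinary and control groups. That also stands. It leaves hospital and era as routes to imbalance, and it does not help comparisons between strategies.

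A reader might infer a one-directional bias by counting only residual nidi that MRI misses. Assumed miss rates of 10 to 30%, residual shares of 20 to 40% and modality gaps of 20 to 40 points give 0.1 × 0.2 × 0.2 = 0.4 to 0.3 × 0.4 × 0.4 = 4.8 points. That calculation assumes MRI never reports residual nidus falsely. Once p(1 − sp) exceeds (1 − p)(1 − se), the sign reverses, as in the last row of the table.

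A reader might also treat the absence of a rule for discordant DSA and MRI readings as a defect. An article may leave that to the full protocol or imaging charter, so it is not counted here.

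Finally, it is tempting to let DSA decide and to set MRI-only patients apart. The documents do not settle that choice. If receipt of DSA depends on treatment, hospital or era, the DSA-read subset is selected, and misclassification would be exchanged for selection bias.

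**Conclusion.** The contradiction is real and concerns one secondary outcome at one time point. Under *or*, nothing in the article keeps the reading modality comparable across strategies or between the multidisciplinary and control groups, so their obliteration comparisons are open to bias.

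The documents do not show that such a bias exists, how large it is or which way it runs, because they report neither modality use by group nor MRI accuracy. Under the assumptions above it spans −0.8 to +2.5 points for a 20-point gap in DSA use. It spans −2.0 to +6.25 points for a 50-point gap, which is an extreme case. The primary outcome, mRS at 3 years, is untouched. This should be corrected, but it does not threaten the registry's main analysis.

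**What to change.** Reconcile Table 1, Imaging data collection, Follow-up assessment and Outcomes measurements to a single rule for how the 3-year obliteration outcome is read, applied identically in every group. Record the modality behind each patient's reading, and tabulate it by treatment and by group.

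Add two sensitivity analyses that hold modality constant and use only imaging already scheduled:

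- the MRI reading in all patients, which is feasible because the named sequences are mandatory at 3 years;
- the DSA reading where a 3-year DSA exists.

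The cost is wording, one recorded field and a little more analysis. The DSA-read subset will be smaller and possibly selected, so it should not by itself replace the main analysis. Recruitment is still open, and only 42.4% of the multidisciplinary patients not lost to follow-up had completed 3 years, so the rule can be set before most of that group reaches the endpoint.

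### The subsequent-hemorrhage definition requires CT evidence, so symptomatic bleeds shown only on MRI and rupture deaths without a CT do not count, even after committee review

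*Protocol article*

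**What the plan says.** Under Outcomes measurements, subsequent hemorrhage is a secondary outcome at 3 years, with this definition: "The subsequent hemorrhage is defined as intracranial hemorrhage that could be attributed to AVM rupture with symptomatic and CT evidence". The rule at presentation, under Demographic and clinical characteristics, is the same: "The hemorrhagic presentation is defined as hemorrhage attributable to AVM rupture with symptomatic and CT evidence". Neither section accepts MRI, autopsy or a death record in place of CT.

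Under Follow-up assessment, three further statements matter:

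- Routine imaging: "The MATCH study will conduct routine imaging follow-up by MRI".
- Source data: "Medical records and imaging examination data will be collected for suspected individuals with cerebral vascular events". Neither the imaging modality nor the setting is restricted.
- Review: "An independent final review committee will assess suspected vascular events without hospitalization".

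Imaging data collection makes a blood-sensitive MRI sequence part of the mandatory set: "susceptibility-weighted imaging (SWI), three-dimensional time-of-flight MR angiography (3D-TOF MRA) are included as mandatory sequences at baseline, 3-month", and likewise at the later visits. Images are analyzed by an Imaging Committee that is part "of the MATCH Research Organizing Committee"; it is not described as adjudicating events.

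Under Statistical analysis, subsequent hemorrhage is the outcome for the Cox, competing-risk or nested case-control analyses, the Kaplan–Meier plots and the ROC assessment of the prediction models.

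**The concern.** An outcome definition should recognize every event of the kind it is meant to measure, using the evidence the study will hold. Here CT is a necessary condition, while the modality used for routine follow-up is MRI. The same Outcomes measurements section accepts either DSA or MRI for obliteration, so the authors do name a second modality where they intend one.

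The committee assignment makes this sharper. Events without admission are plausibly those for which a CT is often missing, and they are the ones sent for independent review. The definition gives that committee no way to turn a convincing event without CT into a counted one.

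What is at stake is mainly an absolute rate. Natural history is a rate per year, and missed events lower it even when they are missed equally everywhere. In the time-to-event analyses, a rupture death without CT would be handled as a competing event or a censored observation instead of a hemorrhage. The rupture models would be fitted to the same incomplete outcome.

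**Working it through.** **Step 1. Apply the definition to each type of event.**

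| Event | Symptoms | CT | Counts as written? |
|---|---|---|---|
| Bleed with CT, patient survives | yes | yes | yes |
| Bleed with CT, patient dies | yes | yes | yes |
| Bleed confirmed on MRI only | yes | no | no |
| Rupture death with no CT | yes or unknown | no | no |
| Silent blood products on routine MRI | no | no | no, and reasonably so |

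The problem is confined to the third and fourth rows.

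**Step 2. Set the definition beside the review rule.** The committee receives suspected events without hospitalization. A death at home, or a symptomatic patient seen only at an outpatient MRI, falls there. The article does not say what evidence the committee may accept, and the only stated criterion is symptoms plus CT. The two sections need to be reconciled.

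**Step 3. Direction of the effect.** Let m be the share of true symptomatic ruptures without CT.

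- Absolute rate: recorded rate = true rate × (1 − m). It falls for any m above 0.
- Comparison of groups: recorded risk ratio = true risk ratio × (1 − m₁)/(1 − m₀), where m₁ and m₀ are the shares in the multidisciplinary and control groups. With m₁ = m₀ the ratio is unchanged; it moves only if the shares differ.

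So the natural-history rate is affected with certainty once m > 0. The group comparison is affected only under an extra condition on which the documents are silent.

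**Step 4. An illustrative size.** The article contains no event calculation for this outcome, so there is no figure to reproduce. Inputs:

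- 491 conservatively managed patients of 3241 (Table 3)
- untreated rupture rate of 1–3% per year (Background)
- 3 years, the outcome time, with complete follow-up assumed
- m = 5–20%, an assumption, since the documents give no share

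Expected bleeds = patients × years × rate:

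- 491 × 3 × 0.01 = 14.7, about 15
- 491 × 3 × 0.03 = 44.2, about 44

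Uncounted bleeds = expected × m:

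- lowest: 14.7 × 0.05 = 0.7, about 1
- highest: 44.2 × 0.20 = 8.8, about 9

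The untreated rate cannot be carried over to the other 3241 − 491 = 2750 patients (2750/3241 = 85%), who were treated.

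**The case against.** The best defense has four parts.

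**Unscheduled imaging.** A symptomatic bleed is imaged when it happens, so the lack of scheduled CT after discharge in Table 1 says little about whether an acute bleed gets one. This stands, and the point does not rest on Table 1. It bears on how large m is; it does not supply a rule for the events that lack CT.

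**Deliberate strictness.** Requiring symptoms keeps silent MRI findings out and matches the rule at presentation. This also stands. The request here keeps the symptom requirement and concerns only the modality.

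**The unshown full protocol.** Adjudication details normally sit in a charter. That is fair for the committee's procedures, but less so for the outcome definition, which the article states as a complete rule.

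**Limited reach.** The primary outcome, mRS at 3 years, does not use the CT rule. That is correct.

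Four stronger readings are tempting and are not supported:

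- *That fatal bleeds are lost.* Nothing excludes a fatal bleed that has a CT. Only deaths without one fail.
- *That hospitalized bleeds are outside independent review.* The article states review for non-hospitalized events; it does not say that others are excluded. Nor does it give the share of bleeds that are hospitalized.
- *That 97 to 292 bleeds are at issue* (3241 × 3 × 1–3%). This applies an untreated rate to a cohort of which 85% was treated.
- *That relabelling bleeds as procedural pulls a true risk ratio of 1.0 to 0.8–0.9.* That follows only from assuming that 10–20% are relabelled in one group alone. A bleed called procedural should also still appear in the complication rate, itself a secondary outcome.

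**Conclusion.** The point holds in a limited form. As written, symptomatic bleeds shown only on MRI and rupture deaths without CT do not meet the definition, and committee review cannot change that. The consequence is a downward bias in the hemorrhage rate behind the natural-history objective and in the outcome used for the prediction models. A bias in the comparison of multidisciplinary and control patients does not follow unless the share without CT differs between them.

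The size is unknown. The 1 to 9 bleeds among 491 conservatively managed patients rest on the quoted 1–3% annual rate, full 3-year follow-up and an assumed 5–20% without CT; the last of these has no source in the documents. The change is worth making, but it concerns a secondary outcome and leaves the primary outcome untouched.

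A secondary matter is one of clarification. Attribution to rupture requires judgement after treatment, because hemorrhage is also listed among perioperative complications. The groups are not randomized, and no masking of event assessment is stated. A charter that is not shown may already deal with this.

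**What to change.** 1. Define subsequent hemorrhage as symptomatic intracranial hemorrhage attributable to AVM rupture and shown on CT, MRI or autopsy. Deaths or events without imaging are classed as probable rupture or not by the existing independent committee.
2. Apply the definition identically to both groups and to all events recorded since 2011, using the records and imaging already collected for suspected events. A forward-only change would create the differential ascertainment it should avoid: 2181 single-disciplinary patients have already completed 3 years, against 191 multidisciplinary patients (Table 3).
3. Report the CT-confirmed count as a sensitivity analysis, so that results under the present rule remain available.
4. State whether the committee also classifies hospitalized post-treatment bleeds as rupture or procedural complication, with multidisciplinary status masked.

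The cost is a change of wording plus retrospective re-classification of suspected events over about a decade, which is real work even though the source data are collected. The drawback is a few less certain events, which item 3 makes visible. Item 4 adds committee workload only if such review is not already in place.
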